### Setting

Primary care centers of the Sexual and Reproductive Health Care (ASSIR; *Atenció a la Salut Sexual i Reproductiva*) of Mutua Terrassa, Barcelona (Spain), with approximately 1,700 pregnancies per year.

### Sample and sample size

Pregnant women ≥18 years followed in the primary care centers of the Sexual and Reproductive Health Care of Mútua Terrassa, Barcelona (Spain) will be invited to participate. 

There are very few scientific publications on which to base our assumptions about the differences that the intervention will produce in the results of the scales that measure anxiety in pregnant women. In a previous interventional work published using a mindfulness program to evaluate changes in the EDPS scale in pregnant women, the authors report after the program a mean difference between the two groups of study (intervention and control) of -2.56, with a standard error (SE) of 0.72 [36] From that, the standard deviation (SD) has been calculated as: SE=SD/Root(n), so SD=SE*Root(n). In this case, as the n was different in both groups (51 and 45), we use the minimum of both (45), obtaining a joint SD of 4.83. 

Assuming a power of 80% to detect differences in the contrast of the null hypothesis H_0_: μ_1_=μ_2_ by means of a bilateral T-Student test for two independent samples, a significance level of 5%, and assuming a mean difference between both groups of -3.5 and a SD of both groups of 4.83 units, it will be necessary to include 31 women in the non-intervention group and 31 women in the intervention group, totaling 66 patients in the study. Considering that the expected drop-out rate is 5%, it would be necessary to recruit 70 women (35 in each group). 

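### The planning SD of 4.83 comes from applying a one-mean formula to the standard error of a between-group difference; the printed figures imply 3.52, and the target of -3.5 is unexplained, but the two departures offset

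*Protocol article*

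**What the plan says.** In the protocol article, under Sample and sample size, the planning inputs come from one earlier trial of a mindfulness programme in pregnancy, which is said to have reported "a mean difference between the two groups of study (intervention and control) of -2.56, with a standard error (SE) of 0.72" on the EPDS. The article states that it recovers the SD by multiplying the standard error by the square root of n. The group sizes were 51 and 45, and on its choice of n it says: "we use the minimum of both (45), obtaining a joint SD of 4.83".

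It then computes the sample size "assuming a mean difference between both groups of -3.5 and a SD of both groups of 4.83 units", using a two-sided two-sample t-test at 5% with 80% power. The result is 31 women per group, and 35 per group are to be recruited. The section does not explain the move from -2.56 to -3.5. It also does not say whether the 0.72 is from an unadjusted comparison or from a model.

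**The concern.** The article itself presents 0.72 as the standard error of a difference between two groups, yet converts it as if it were the standard error of one group's mean. The standard error of a difference carries sampling error from both groups, so the one-mean formula attributes too much variability to each woman's score and overstates the SD. Having to choose between 51 and 45 is a sign of the problem, because the two-sample formula uses both.

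The target difference is a second, separate matter. The cited trial is offered as the basis for the assumptions, but the effect actually used is larger than the one cited, and nothing links them.

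At stake is whether the stated power follows from its source. Anyone who corrects only one of the two inputs reaches a very different view of the trial's size. The SD of 4.83 could also be carried forward as a published planning value.

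**Working it through.** **Inputs**, all from Sample and sample size: cited difference -2.56; standard error 0.72; cited group sizes 51 and 45; planning difference -3.5; planning SD 4.83; two-sided 5% t-test; 80% power; 31 per arm.

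**1. Reproduce the plan's SD.** SD = SE × √n = 0.72 × √45 = 4.83. This matches the article.

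**2. Reproduce the plan's sample size.** With difference 3.5 and SD 4.83, the exact (noncentral t) calculation gives 31 per arm, with power 80.2%. The normal approximation gives 30. The stated 31 per arm therefore follows from the stated inputs.

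**3. Convert the standard error of a difference.** With a common SD, SE = SD × √(1/n1 + 1/n2), so

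SD = 0.72 / √(1/51 + 1/45) = 0.72 / √0.04183 = 0.72 / 0.2045 = 3.52.

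Ratio: 4.83 / 3.52 = 1.37. Using 45 for both groups gives 0.72 / √(2/45) = 3.42, so the choice of the smaller group is not the cause. The cause is the missing second group, a factor of √2 at equal group sizes.

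**4. Check in reverse.** An SD of 4.83 in groups of 51 and 45 would give SE = 4.83 × 0.2045 = 0.99, not the 0.72 the article reports.

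**5. Compare the target with the cited effect.** 3.5 / 2.56 = 1.37, which is 37% larger.

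**6. Compare the standardised effects.** As planned: 3.5 / 4.83 = 0.725. With the cited effect and the corrected SD: 2.56 / 3.52 = 0.727. The two departures are almost the same size and cancel in the ratio that determines n.

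**7. Power at the corrected SD** (exact t, two-sided 5%):

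| Difference | SD | Power at 31 per arm | n per arm for 80% |
|---|---|---|---|
| -3.5 | 4.83 (as printed) | 80.2% | 31 |
| -2.56 | 3.52 | 80.4% | 31 |
| -3.5 | 3.52 | 97.1% | 17 |

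For -2.56 at SD 3.52, power is 82.9% with 33 evaluable per arm and 85.1% with 35.

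**The case against.** The strongest case on the other side is that nothing in the trial changes. The stated calculation reproduces. Taken alone, the SD error is conservative, since it raises the requirement for -3.5 from 17 to 31 per arm. With the cited effect and the corrected SD, 31 per arm is again the answer. This stands, and it limits how serious the point is.

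A target difference also need not equal one earlier estimate. The article says that little has been published to guide its assumptions, and a condensed article may leave out a rationale. This stands too: -3.5 is an unexplained planning assumption, and calling it a mistake would go beyond the text.

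A reader might infer that the trial is badly underpowered, because -2.56 with SD 4.83 gives only 53.7% power at 31 per arm and would need 57 per arm for 80%. The documents do not support that reading. It pairs the cited effect with the very SD that the cited standard error contradicts. It would matter only if the true SD were near 4.83 for some other reason, and nothing in the article establishes that.

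Finally, 3.52 is itself conditional. If the 0.72 came from a model adjusted for baseline or other covariates, 3.52 is a residual SD and the raw SD could be larger. The sample size rests on an unadjusted t-test, and the tests named under Quantitative data analysis are also unadjusted comparisons. A residual SD would not fit them. This stands as a limit on the remedy, but it does not rescue 4.83: the one-mean formula is wrong for a difference whether or not the standard error is adjusted.

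**Conclusion.** The derivation of the planning SD is wrong as written. On the printed figures the SD is 3.52, so 4.83 is overstated about 1.37-fold. The target of -3.5 is a separate assumption, 37% above the only effect cited, with no reason given. The two offset, so no loss of power is shown: about 80% for -2.56 and about 97% for -3.5, both at SD 3.52 with 31 evaluable women per arm.

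This rests on 0.72 being the unadjusted standard error of the between-group difference, on a common SD in both groups, and on the stated two-sided 5% t-test. The formula error is certain on the article's own wording. The value 3.52 depends on the first assumption, which the article does not settle. The point concerns the correctness of the stated justification and ranks below a must-fix.

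**What to change.** - Replace the one-mean conversion with SD = SE / √(1/n1 + 1/n2).
- Check in the cited source whether the 0.72 is unadjusted. If it is, restate the SD as 3.52. If it is model-adjusted, take the raw group SDs from the source and recompute power with those, because 3.52 would not fit the planned unadjusted test.
- State the power that matches the chosen target difference. At SD 3.52 and 31 evaluable women per arm, this is about 80% for -2.56 or about 97% for -3.5.
- If -3.5 is kept, give the reason for it.

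The cost is one look at the cited source and a few rewritten sentences. On the printed figures, no change in enrolment is needed. If the source proves to be model-adjusted, that conclusion has to be rechecked against the raw SDs.

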## Design and methods

This will be a two-arm prospective, randomized, parallel-controlled clinical trial. 70 women will be recruited and screened during their pregnancy. Women showing positive scores in an early mental health screening at weeks 12–14 of pregnancy (screening tests: two Whooley questions, two Generalized Anxiety Disorder-2 [GAD-2] questions, self-administered Edinburg Postnatal Depression [EPDS]) will be randomly allocated to an intervention or control group.

If the answer to all four initial questions is negative, we will consider the screening negative. If the answer is positive to any of the four questions, the screening is positive, and it is recommended to administer the EDPS. EDPS is negative if score < 13 or item 10 is negative. EPDS is positive if score < 13 and item 10 positive or ≥ 13. If the answer is positive to any of the four questions, but the EDPS is between 9–13, they are candidates to enter the study.

The usual monitoring of pregnancy control will be carried out at the center (including anamnesis, blood tests, serology and urine tests, among other assessments), regardless of the group. In a first phase (weeks 12–14 of gestation), the following tests will be performed in both groups: EPDS, State Trait Anxiety Inventory (STAI), Symptom Checklist-90-Revised (SCL-90-R), and Temperament and Character Inventory-Revised (TCI-R). The intervention group will receive the usual mentioned follow-up pregnancy monitoring plus an *e*-*health* (virtual reality) intervention. The control group will receive the usual mentioned follow-up pregnancy monitoring, without the *e*-*health* intervention. In a second phase (6 weeks after), the following assessments will be repeated in both groups: EPDS, STAI, and SCL-90. In the case of the intervention group, a questionnaire on the usability of the technology will also be passed. At the end of the pregnancy all women will receive a questionnaire on their satisfaction with the follow-up of their pregnancy, including questions on equipment, accessibility, organization of the consultation and care and competence of the staff (28 questions in total). Providing a control group that receives the same monitoring control establishes whether the technological low-intensity intervention accounts for the results. The involvement of midwives in collaboration with mental health nurses will maximize the translation of research findings into practice.

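### The two groups of 31 add to 62, not 66, so the 70 carries more than the stated 5% drop-out allowance; and the design section counts those 70 women as screened, not randomised

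*Protocol article*

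**What the plan says.** The sample size calculation (protocol article, Sample and sample size) is for the EPDS, compared "by means of a bilateral T-Student test for two independent samples" at a two-sided 5% level. The other inputs are:

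- "Assuming a power of 80% to detect differences";
- "assuming a mean difference between both groups of -3.5";
- "a SD of both groups of 4.83 units".

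From these the article concludes that "it will be necessary to include 31 women in the non-intervention group and 31 women in the intervention group, totaling 66 patients". It then takes an expected drop-out of 5% and states that "it would be necessary to recruit 70 women (35 in each group").

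The opening of Design and methods uses the same 70 differently: "70 women will be recruited and screened during their pregnancy". The next sentence says that the women with positive scores on the early mental health screen are the ones randomised. Inclusion criteria and Recruitment protocol and randomization procedure narrow this to women with a positive screen and an EPDS score of 9 to 12. The recruitment section also obtains consent before the initial screening.

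**The concern.** Two things in the text do not fit together.

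First, the printed total is not the sum of the two printed group sizes, and the final target of 70 is built on that total. A reader cannot tell whether 62 or 66 women are meant to be evaluable, or what loss the 70 really covers. Both figures will be checked against the CONSORT flow that the article promises.

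Second, 70 is the number allocated in one section and the number screened in another. The two agree only if every screened woman qualifies. The sum affects only the stated bookkeeping. The second point could affect power, but only if someone applied the design sentence as written and stopped after screening 70 women.

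**Working it through.** **Inputs** (all from Sample and sample size): difference 3.5; SD 4.83 in both groups; two-sided alpha 0.05; power 0.80; two-sample t-test; equal groups; drop-out 5%. The standardised difference is 3.5/4.83 = 0.725.

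**Step 1: reproduce the group size.** By the normal approximation, n per group = 2 × (1.960 + 0.842)² / 0.725² = 29.9, so 30. The exact power of the t-test uses the noncentral t distribution with 2n − 2 degrees of freedom and noncentrality 0.725 × √(n/2):

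| n per group | Power |
|---|---|
| 30 | 78.8% |
| 31 | 80.2% |
| 33 | 82.6% |
| 35 | 84.8% |

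The smallest n reaching 80% is 31, so the article's group size is reproduced.

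**Step 2: the total.** 31 + 31 = 62. The article prints 66.

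**Step 3: the drop-out allowance.**

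- Applied once to 62: 62/0.95 = 65.3, so 66 (33 per group).
- Applied again to 66: 66/0.95 = 69.5, so 70 (35 per group).
- Multiplying by 1.05 instead gives 65.1 and 69.3, which round up to the same 66 and 70.

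Two 5% inflations reproduce both printed figures under either convention. The allowance actually contained in 70 is 1 − 62/70 = 11.4%.

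**Step 4: effect of the slip on power.** 70 × 0.95 = 66.5, so about 66 women complete (33 per group), with power of about 82.6%. The trial is slightly larger than its inputs require.

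**Step 5: 70 read as the number screened.** To have 62 evaluable women out of 70 screened, 62/70 = 89% would have to qualify, consent to allocation and complete, with no loss at all. The article gives no rate for a positive screen combined with EPDS 9 to 12, so the shortfall cannot be estimated. As an illustration only, assume 65% qualify; this is the largest anxiety prevalence that the Background quotes, for some populations. Then 70 × 0.65 = 45.5, about 45 randomised. Power is 65.1% with 22 per group and 66.1% with 22 and 23, before any drop-out.

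**The case against.** The strongest reply has three parts.

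*The cause is not shown.* The article does not say where 66 came from. A misprint of 31 for 33 would also give 2 × 33 = 66 and then 70. This stands, so double inflation can only be called the apparent cause. It is the likelier one, because the stated inputs give 31 and not 33. The error in the total does not depend on the cause.

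*The slip does no harm.* This also stands. The group size is right, the target of 35 per group is internally consistent, and the surplus raises power. The 5% is an expected rate and is not itself wrong; the 70 simply covers more than 5%.

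*Nobody will stop at 70 screened.* A reader might infer from the design sentence that the trial is planned to be underpowered. The rest of the article does not support that:

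- the sample size section places the 70 as 35 in each group;
- all women followed in the service are to be invited, with about 1,700 pregnancies a year (Setting) and 24 months of recruitment (Discussion);
- the analysis section plans to report the percentages eligible, consenting and entering randomisation, which presupposes that more women are assessed than randomised.

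So the design sentence is most likely loose wording. What remains is that it contradicts the sample size section and should be aligned with it.

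The Background prevalences also should not be treated as bounds on eligibility. They describe anxiety or depression in other populations, not a positive four-question screen with an EPDS score in a narrow band.

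**Conclusion.** The point holds as two corrections to the text.

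1. The total before drop-out is 62, not 66. A single 5% allowance leads to 66, and the printed 70 contains 11.4%. Taken alone this errs on the safe side, at about 82.6% power after 5% loss, given the article's own difference and SD. That SD was derived from a published standard error; its derivation is not examined here.
2. The sections disagree on whether 70 counts women screened or women randomised. Only the randomised reading is consistent with the power calculation. On the literal screened reading, the stated power needs 89% of screened women to qualify with no loss. The figure of about 65% power is an illustration under an assumed 65% qualifying rate, not a prediction.

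The documents do not support a claim that the trial as planned is underpowered, or a firm statement of how the 66 arose.

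**What to change.** In Sample and sample size, replace the total with 62 evaluable women (31 per group). Then choose one of two consistent statements:

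- 66 women randomised (33 per group), allowing for 5% drop-out; or
- 70 women randomised (35 per group), which covers up to 11% loss.

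The first follows directly from the stated 5%. The second keeps the present target and should say openly that it exceeds the expected loss.

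In Design and methods, say that the chosen number of women will be randomised and that screening continues until it is reached.

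The cost is a few figures and one sentence. Neither option needs more than the 70 women already planned for allocation.

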### Inclusion criteria

All women who control their pregnancy in the primary care centers of the Sexual and Reproductive Health Care (ASSIR; *Atenció a la Salut Sexual i Reproductiva*) of Mutua Terrassa, Barcelona (Spain) will be invited to participate. The ASSIR is a support structure for primary care and is located between primary and specialized care, with the aim of promoting, encouraging and coordinating activities for comprehensive sexual and reproductive health care for women. The women must present a positive value in the mental health screening performed at the beginning of the pregnancy (weeks 12–14 of gestation). Women scoring positive (EPS 9–12) will be randomized to either the control or intervention group. The women must be able to have a good verbal and written understanding of Spanish and be ≥ 18 years old.

### Exclusion criteria

Women with diagnosed psychiatric pathology who are already being followed by the mental health team will be excluded from the study. Women victims of gender-based violence who tested positive in the partner violence screen (PVS) were also excluded [37].

### Recruitment protocol and randomization procedure

The research will follow a pre-established recruitment protocol following ethical guidelines for human research. The selection of the women will be done consecutively, during the visit 12–14 months of gestation. The staff will be explained on the project an invite eligible pregnant women to contact to the research midwife. After obtaining informed consent, women will be invited to provide contact details and complete an initial screening plus a full questionary about different sociodemographic and clinical aspects. Women who will answer "yes" to any of the four questions of the screening test, and who in the EDPS will score between 9 and 12, will be candidates for the study. The questionnaire responses will then be evaluated and the women will be contacted and, with their permission, randomly assigned to one of the two treatment groups. The principal investigator will create a randomisation list with the computer epidemiological program EPIDAT (Epidat 4.2) after participant’s written consent and not blinded to the woman’s allocation.

Randomisation of the study subjects will be masked. Women who enter the study will be scheduled for an extra visit with the midwife between weeks 15 and 17 of gestation. The woman who will be assigned to the control group will be informed that the follow-up will be as usual. The women in the interventional group will receive information about the intervention using *e-health* support (immersive virtual reality).

Participants will also be provided with a contact email address if they require additional support.

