### Control group

Pregnant women in the control group will be cited for an extra visit, where they will be given the following scales: STAI, SCL-90 and TCI-R. These women will undergo the usual monitoring of pregnancy control at the center by the midwife, according to the Protocol for Monitoring Pregnancy of the Generalitat de Catalunya [45]. The women will be called to back after 6 weeks to go through the same scales again (except the TCI-R), and the pregnancy satisfaction questionnaire.

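### Allocation concealment is not secured, and the plan gives two conflicting times for the baseline STAI and SCL-90, one of them after assignment

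*Protocol article*

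**What the plan says.** All references are to the Protocol article.

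- **The list** (Recruitment protocol and randomization procedure): "The principal investigator will create a randomisation list with the computer epidemiological program EPIDAT (Epidat 4.2"), once the woman has consented in writing. The same sentence describes the investigator as "not blinded to the woman’s allocation".
- **Masking** (same section, start of the next paragraph): "Randomisation of the study subjects will be masked". It does not say who is masked or from what.
- **Order of events** (same section): once the screening answers have been assessed, "the women will be contacted and, with their permission, randomly assigned to one of the two treatment groups". Women in the study then have an additional midwife appointment at weeks 15–17.
- **Disclosure** (same section): "The woman who will be assigned to the control group will be informed that the follow-up will be as usual". Women in the other arm are told about the virtual reality programme.
- **Baseline, version 1** (Design and methods): in a first phase at weeks 12–14, "the following tests will be performed in both groups: EPDS, State Trait Anxiety Inventory (STAI"), with SCL-90-R and TCI-R in the same list.
- **Baseline, version 2** (Control group): women already in that arm attend the extra visit, "where they will be given the following scales: STAI, SCL-90 and TCI-R". After six weeks the scales are repeated, except TCI-R.
- **Use of the scores**: Outcome measures makes EPDS, STAI and SCL-90 primary. Quantitative data analysis compares pre-to-post effect sizes between the arms.

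**The concern.** There are two linked weaknesses in the order of events around allocation.

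First, the only person named as making the list is the trial's lead, who is unblinded and makes it after consent. Screening scores are known before a woman is contacted and asked for permission, so there is a decision point just before assignment. Unless the next assignment is hidden from whoever acts at that point, enrolment can become selective. The word *masked* does not answer this, because the text does not say what it means.

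Second, if the first STAI and SCL-90 are completed after a woman knows her arm, they are no longer clean baselines. The Measures section itself describes the state part of STAI as capturing a transitory emotional state. Hearing that one will, or will not, receive a new programme could plausibly move it. A baseline that moves differently by arm enters any pre-post comparison, and a true pre-assignment score cannot be recovered later.

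**Working it through.** The plan states no figure on this point, so the check sets the sections side by side and follows an altered baseline through to the estimate.

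**1. What can *masked* mean?**
- *Participants are blinded.* This is ruled out by the same paragraph, where each woman is told what her group will receive.
- *The list-maker is blinded.* This is ruled out by the sentence before it.
- *The upcoming assignment is hidden from those enrolling.* This is possible and compatible with an unblinded list-maker, but the text does not say so.

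Only the third reading survives, and the article does not state it.

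**2. When are STAI and SCL-90 first taken?**
- Version 1 (Design and methods): weeks 12–14, both groups.
- Version 2 (Control group, read with Recruitment protocol and randomization procedure): the extra visit at weeks 15–17, for women already assigned to control. Because the scales are repeated after six weeks, the extra-visit scores serve as the baseline.
- Data collection and management lists a pre-intervention time point separate from recruitment, which fits version 2 better.
- If the six weeks run from the baseline, follow-up falls at weeks 18–20 under version 1 (12 + 6 to 14 + 6) and at weeks 21–23 under version 2 (15 + 6 to 17 + 6). The two versions therefore describe different schedules.
- No section says whether, at the extra visit, the scales come before or after the woman is told her arm. The text states version 2 only for controls. The study-design figure, which may settle this, is not shown.

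**3. How would a shifted baseline reach the result?**

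Let I and C denote intervention and control. The pre-post contrast is

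D = (Post_I − Pre_I) − (Post_C − Pre_C).

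If knowledge of the arm moves the mean reported baseline by s_I and s_C, then

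D_observed = D_true + (s_C − s_I).

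- Equal shifts cancel. Unequal shifts pass in full into the contrast.
- Adjusting for baseline with slope β does not remove the error; it becomes β(s_C − s_I).
- Lower scores are better, so a benefit is a negative D. If only controls report more distress on learning their arm (s_C > 0, s_I = 0), the benefit is understated. If they report less (s_C < 0), it is overstated. The direction is therefore open.
- The documents give no value for s_I or s_C, so no size can be computed.

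**4. Which outcomes are exposed?**
- STAI and SCL-90 are exposed under version 2: they are primary, self-reported and analysed pre-post.
- EPDS is not exposed. A score of 9–12 is an entry condition, so a pre-assignment score exists for every woman and its shift is zero.
- The sample size is also untouched. It rests on EPDS and an independent-samples t-test, which uses no baseline.

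**The case against.** The strongest defence has four parts.

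- **Concealment may be intact.** Knowing an allocation differs from foreseeing it. Selection is consecutive, staff invite women to contact a research midwife, and the text does not say that the principal investigator enrols women or that recruiters see the list. If an assignment is generated only after a woman consents, nobody could have known it when she consented. This stands. A reader might infer that allocation is not concealed, but the article shows only that concealment is not secured.
- **Masked and unblinded can coexist.** If *masked* means that the sequence is hidden from recruiters, there is no strict contradiction. This also stands. Nor does the article claim to be a blinded trial; it applies the word to randomisation only. What remains is an undefined term beside a sentence that invites doubt.
- **Design and methods places the scales before the extra visit.** A reader might infer from the Control group section that baselines are certainly taken after allocation. That is one of two conflicting versions, stated for one arm. The conflict itself is not answered.
- **This is a journal article.** The mechanics of concealment, such as envelopes or locked forms, are commonly left to the full protocol, so their absence is no finding. The point rests instead on what the article does state: who makes the list and when, an undefined *masked*, and two baseline times.

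The investigator's role as e-mail contact and recipient of technical alerts begins after allocation and adds nothing on concealment.

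**Conclusion.** The point holds in a limited form. As written, an unblinded principal investigator makes the list after consent, *masked* is undefined, and two sections disagree on when STAI and SCL-90 are first measured. If the Control group version is followed and disclosure comes before the questionnaires, the pre-post contrast on two of the three primary scales can be biased by s_C − s_I.

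This rests on two assumptions: that the extra-visit scores serve as the baseline, which the six-week repeat implies, and that knowledge of the arm affects the two arms' answers differently, which is plausible but not shown.

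The size of the bias cannot be derived from the documents. A reader might try to bound it from the width of the EPDS entry band. That does not work: it would need the arms to sit at opposite ends of the band, which nothing in the text suggests, and EPDS is not the scale with the baseline-timing problem.

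The matter should be settled before enrolment, because a baseline taken too late cannot be repaired in analysis.

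**What to change.** 1. Reconcile Design and methods, Recruitment protocol and randomization procedure, and Control group so that STAI, SCL-90-R and TCI-R are completed in both groups before the arm is assigned or disclosed. State the same timing in each section.
2. Have the Epidat list generated once, before the first woman is enrolled, by an existing colleague with no part in recruitment or follow-up. Keep it hidden from those who enrol.
3. Replace *masked* with wording such as *allocation concealed; open-label after assignment*.

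The cost is a one-off task for a colleague, a fixed order of events at visits already planned, and a change of wording. No extra visit, instrument or participant is needed.
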